### Sample size {14}

A cluster randomized trial with an average cluster size of 37 incident participants over 2 years requires 42 clusters to achieve 80% power to detect a 20% reduction in the hazard of a first PD-related infection with the log-rank test in a cluster-randomized design at a type I error rate of 5%. This translates to approximately 650 events from approximately 1500 participants. The power calculation assumes 53% of the participants in the control group remain infection-free (data derived from HONEYPOT trial [32]) and an intra-cluster correlation coefficient of 0.001. Average cluster size is based on data from eligible Australian and New Zealand PD units in 2014–2015. Sample size calculations were performed using Power Analysis and Sample Size (PASS) Version 15.

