## Statistical methods

### Statistical methods for primary and secondary outcomes {20a}

Data will be analyzed at the patient level. Patient and treatment characteristics will be presented by study group using descriptive statistics. The primary outcome (coded as yes/no) and follow-up time (censored if < 24 months) will be displayed using Kaplan–Meier survival curves by group and by center size. Survival estimates of the treatment groups will be compared using the log-rank test for clustered data. Cox regression models with standard errors to allow for non-independent observations due to clustering will be used to assess the effect of the intervention on the primary and secondary outcomes. The models will be adjusted for cluster size category and country. The proportional-hazards assumption will be tested for each model. All data will be analyzed on an intention-to-treat basis with *p*-values less than 0.05 taken to indicate statistical significance.

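### With 42 clusters and four cluster-level adjustment terms, the Cox hazard-ratio intervals will be too narrow unless the clustered variance gets a small-sample correction and a t reference

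*Protocol article*

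**What the plan says.** Statistical methods {20a} applies two procedures to the primary outcome. For the first, "Survival estimates of the treatment groups will be compared using the log-rank test for clustered data". The second also serves the secondary outcomes: "Cox regression models with standard errors to allow for non-independent observations due to clustering will be used to assess the effect". These models adjust for cluster size category and country. One threshold, p below 0.05, covers everything, and neither procedure is named as the one that decides the primary outcome.

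Sample size {14} rests on the log-rank test for a cluster design with a 5% type I error: the trial "requires 42 clusters to achieve 80% power to detect a 20% reduction in the hazard of a first PD-related infection". The calculation takes an "average cluster size of 37 incident participants over 2 years" and an intra-cluster correlation (ICC) of 0.001. Sequence generation {16a} randomises clusters 1:1 within strata of country and four size categories.

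The article does not name the variance estimator, a finite-sample correction or a reference distribution for the Cox models.

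**The concern.** The standard way to give a Cox model cluster-allowing standard errors is the cluster sandwich with a Wald z-test. That variance is justified for a large number of clusters. Here there are about 21 per arm, and the model carries five cluster-level terms: treatment, three for size category and one for country. Each such term uses up information between clusters, and the plain sandwich does not allow for it, so its standard errors are too small on average.

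At stake are the width of every hazard-ratio interval, the p-values of the secondary outcomes analysed by Cox regression and, if the Cox model decides, the false-positive rate of the primary result.

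**Working it through.** **1. The plan's own figure reproduces.** Inputs from Sample size {14}: hazard ratio 0.80, 80% power, 5% error (two-sided assumed), 53% of controls infection-free, ICC 0.001, about 1500 participants in 42 clusters.
- Events without clustering (Schoenfeld): 4 × (1.960 + 0.842)² / (ln 0.80)² = 631.
- Mean cluster size 1500/42 = 35.7; design effect 1 + 34.7 × 0.001 = 1.035; events 631 × 1.035 = 653.
- Infection-free share under intervention 0.53^0.80 = 0.602; mean event share 1 − (0.530 + 0.602)/2 = 0.434.
- Participants 653/0.434 ≈ 1504; clusters 1504/35.7 = 42.1.

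This agrees with about 650 events, 1500 participants and 42 clusters. The sample size is not in dispute.

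**2. Rough size of the problem.** Counting six parameters, a plain sandwich is too small by a factor of roughly 36/42 in variance, or √(36/42) = 0.926 in standard error. The effective critical value is 1.96 × 0.926 = 1.81. On a t distribution with 36 degrees of freedom its two-sided tail is 7.8%. Using 1.96 in place of the t(36) value, with no shrinkage, would give 5.8%.

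**3. Simulation under no effect.** From the protocol: 42 clusters (11 in New Zealand, so 31 in Australia), four size categories, stratified permuted blocks and a 53% infection-free share. Assumed, because the article does not give them: the coefficient of variation (CV) of cluster size, light random dropout and the spread of log-hazard between clusters. An SD of 0.05 corresponds to (0.05 × 0.53 × 0.635)² / (0.53 × 0.47) = 0.0011, close to the protocol's ICC. With 4,000 trials per setting, the Monte Carlo error is about 0.3–0.5 points. False-positive rates at that ICC:

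| Cluster-size CV | Adjusted Cox, sandwich, z | Unadjusted Cox, sandwich, z | Adjusted Cox, variance × 42/36, t(36) | Clustered log-rank (two runs) |
|---|---|---|---|---|
| 0.16 | 7.7% | 5.6% | 4.8% | 4.5–4.8% |
| 0.56 | 9.0% | 6.6% | 5.8% | 4.9–5.5% |
| 0.88 | 9.6% | 8.0% | 6.8% | 5.7–5.9% |

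The adjustment terms account for 2.1, 2.4 and 1.6 points in the three rows. Over all settings, including far larger ICCs, the adjusted Cox test ran at 7.7–10.6% and the clustered log-rank test at 4.5–5.9%.

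**4. Sensitivity to the assumptions.** Simulations with other cluster sizes and dropout gave:
- 8.2% (equal sizes) and 8.6% (CV 0.72) at ICC 0.001;
- 7.6–8.7% in a set with size CV from 0 to 0.61, where the log-rank test gave 5.0–5.4%;
- 7.4–8.6% in a further set, where the log-rank test gave 5.2–5.4%.

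No setting brought the plain adjusted test to 5%. With 336 clusters it returned 4.7% (300 trials), so the excess is a few-clusters effect.

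**5. Standard error.** The robust standard error averaged 8–10% below the true SD. One run with uneven clusters gave 0.080 against 0.090, or 11% below.

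**6. Corrected method.** A Mancl-DeRouen-type sandwich with a t reference gave 3.6–5.3% in one set and 3.8–4.5% in another. Simple 42/36 scaling still left up to 7.7% over all settings, so the choice of correction matters.

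**The case against.** The article never says that the standard errors are uncorrected; the plain sandwich with z is an inference from common practice. An article condenses the full protocol, and a statistical analysis plan that is not shown may specify a correction. That stands, and it makes the finding conditional. What the text does fix is 42 clusters, the Cox model, its cluster-level covariates and the 5% threshold, and on the usual reading that combination is anti-conservative.

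A reader might infer that the trial's primary comparison itself runs at 8–11%. The documents do not support this. The procedure described as comparing the groups, and the one behind the 80% power, is the clustered log-rank test, which holds about 5%. The upper end also needs very uneven clusters and an ICC far above 0.001: the 10.6% arose at CV 0.88 and an ICC of about 0.07.

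A reader might also blame the cluster count alone. Without the adjustment terms the rate is 5.6–8.0%, so much of the excess comes from those terms.

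Two further criticisms do not hold as errors. That the log-rank test is not said to use the randomisation strata is detail left out, not a mistake. Reducing the log-rank test to a descriptive role would be a preference, since it is the better calibrated of the two.

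**Conclusion.** The point holds in conditional form. If the adjusted Cox models use the ordinary cluster sandwich with normal critical values, their nominal 5% tests run at about 7.5–10% at the protocol's ICC, and their standard errors are about 8–10% too small. This rests on assumed cluster-size variation and dropout, although the excess persists with equal clusters.

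Whether the primary p-value is affected depends on which test decides, and the article does not say. In one set of simulations the two tests disagreed in 2.5–3.6% of null trials. At least one was significant in 7.7–8.7%, almost the same as the Cox test alone (7.6–8.7%), so nearly every disagreement was a false positive from the Cox model only. A sound log-rank test does not rescue the hazard-ratio interval, which comes from the Cox model, or the Cox-analysed secondary outcomes, for which the article names no other test.

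**What to change.** Before any unblinded analysis:
- For every Cox model, specify a small-sample-corrected cluster sandwich (Mancl-DeRouen or Fay-Graubard type, or a leave-one-cluster-out jackknife). Use a t reference with clusters minus cluster-level parameters as degrees of freedom. Five terms give 42 − 5 = 37; the simulations used the slightly more cautious 36.
- State which single test decides the primary outcome: the clustered log-rank test or the corrected Cox model. Either is defensible.

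If the analysis plan already does both, nothing changes.

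The cost is a few lines of text and code, and no new data. Intervals widen by about 12–15%: 1/0.92 to 1/0.90 for the standard error, times 2.028/1.960 for the t value. If the corrected Cox model decides, the t reference alone lowers power from 79.9% to 77.7% with 1500 participants, or from 81.3% to 79.1% with 42 × 37 = 1554. If the log-rank test decides, the planned power is unaffected.

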**Methods:**

The TEACH-PD trial is a registry-based, pragmatic, open-label, multi-center, binational, cluster-randomized controlled trial. TEACH-PD will recruit adults aged 18 years or older who have not previously undergone PD training at 42 PD treatment units (clusters) in Australia and New Zealand (ANZ) between July 2019 and June 2023. Clusters will be randomized 1:1 to standardized TEACH-PD training curriculum or usual training practice. The primary trial outcome is the time to the first occurrence of any PD-related infection (exit site infection, tunnel infection, or peritonitis). The secondary trial outcomes are the individual components of the primary outcome, infection-associated catheter removal, transfer to hemodialysis (greater than 30 days and 180 days), quality of life, hospitalization, all-cause death, a composite of transfer to hemodialysis or all-cause death, and cost-effectiveness. Participants are followed for a minimum of 12 months with a targeted average follow-up period of 2 years. Participant and outcome data are collected from the ANZ Dialysis and Transplant Registry (ANZDATA) and the New Zealand Peritoneal Dialysis (NZPD) Registry. This protocol follows the Standard Protocol Items: Recommendations for Interventional Trials (SPIRIT) guidelines.

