#### Secondary outcomes

The secondary outcomes are the individual components of the primary outcome: PD infection-related catheter removal, transfer to hemodialysis for greater than 30 days and 180 days, all-cause hospitalization, PD infection-related hospitalization, death from any cause, and quality of life.

A cost-effectiveness analysis from the perspective of the health funder will be completed.

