#### Quality of life

Quality of life is measured using the EuroQol (EQ-5D-5L, Fig. 3: Example of EQ-5D-5L questionnaire (Australian version)), a widely used instrument developed in Europe which assesses quality of life across five dimensions and five levels at baseline and at each 6-monthly visit. The utility value for estimation of quality adjusted life years (QALYs) will be estimated from the EQ-5D-5L scores using the Australian valuation set [34]. Study questionnaires are collected during participants’ regular clinic visits or e-mailed to participants and completed via REDCap or paper forms.

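### Cox regression is assigned to the secondary outcomes without exception, but quality of life is a repeated EQ-5D-5L score with no event defined

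*Protocol article*

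**What the plan says.** The section on statistical methods for primary and secondary outcomes ({20a}) sets out how it will "assess the effect of the intervention on the primary and secondary outcomes". The only tool that it names for this purpose is a hazard model: "Cox regression models with standard errors to allow for non-independent observations due to clustering will be used". It adjusts the models for cluster size category and country and adds: "The proportional-hazards assumption will be tested for each model". No other type of effect model appears in the section, and no outcome is excepted.

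The Secondary outcomes section ends its list with "PD infection-related hospitalization, death from any cause, and quality of life". The Methods paragraph of the abstract also places quality of life among the secondary outcomes: "quality of life, hospitalization, all-cause death, a composite of transfer to hemodialysis or all-cause death, and cost-effectiveness".

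The Quality of life section says that the EQ-5D-5L "assesses quality of life across five dimensions and five levels at baseline and at each 6-monthly visit". Table 1 (Participant study assessments) gives the schedule: a post-training visit labelled as baseline, then months 6, 12, 18 and 24. The only analytic use described for the scores is their conversion to utilities, with an Australian value set, to estimate QALYs.

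**The concern.** A Cox model needs an event and a time at which it happens. The EQ-5D-5L as described yields a score at each of five scheduled visits. It yields neither an event nor a time, so there is no hazard to model and no proportional-hazards assumption to test.

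This is not a gap that an article may leave to the analysis plan. The text does assign a method to this outcome, and that method does not fit it. Two courses remain. The analysis plan may use a different model, in which case it departs from the published method. Or someone must turn the score into an event with a cut-off that the article does not fix. The second course matters more than usual here, because the trial is open-label and the questionnaire is completed by the participants. A threshold chosen late would be hard to defend.

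**Working it through.** The point rests on wording, so the main step is to set the sections side by side.

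1. **Scope of the model.** Section {20a} applies Cox regression to the primary and secondary outcomes. It does not say all of them, but with no qualifier and no second model, that is the plain reading.
2. **Membership.** Quality of life is a secondary outcome in both the Secondary outcomes section and the abstract.
3. **Form of the data.** The Quality of life section and Table 1 give repeated scores at five fixed visits.
4. **Search for an event.** Nothing in the article defines a deterioration, a minimum change, a threshold or a time origin for this outcome.
5. **Other secondary outcomes.** The infection components, infection-related catheter removal, transfer to hemodialysis, hospitalisation and death can each be analysed as time to first event, so the Cox sentence suits them. Cost-effectiveness is given an analysis of its own. The mismatch is therefore limited to quality of life.

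**How many scores are concerned.** The inputs are about 1,500 participants (Sample size), follow-up visits at months 6, 12, 18 and 24 (Table 1), and a minimum follow-up of 12 months with a targeted average of 2 years (Participant timeline).

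- Ceiling, if everyone reaches month 24: 1,500 × 4 = 6,000.
- If everyone reaches only month 12 (visits at months 6 and 12): 1,500 × 2 = 3,000.
- Both counts are before early exits such as transplantation, permanent hemodialysis transfer, death and withdrawal.

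**Check that the sample size is not involved.** With a hazard ratio of 0.80, 80% power, 1:1 allocation and a 5% type I error assumed two-sided, Schoenfeld's formula gives 631 events. The design effect is 1 + (37 − 1) × 0.001 = 1.036, so 631 × 1.036 ≈ 654 events. The event probability is 0.47 in the control arm and 1 − 0.53^0.8 = 0.398 in the intervention arm, mean 0.434. Then 654 / 0.434 ≈ 1,506 participants, and 1,506 / 37 ≈ 40.7 clusters, or 42 when rounded up to an even number. The protocol's figures of about 650 events, about 1,500 participants and 42 clusters are reproduced. They concern the primary outcome only and do not depend on the quality-of-life model.

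**The case against.** The strongest reply is that this is a condensed article. Section {20a} is one paragraph built around time-to-event outcomes, the model for a single patient-reported outcome usually sits in the analysis plan, and no statistician would fit a Cox model to a utility score. As a forecast of what will happen, this is fair: the likely outcome is a different model in the analysis plan, not an invalid result. It does not rescue the sentence, which assigns a model to this outcome instead of staying silent.

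Three stronger readings are tempting, and the document does not support them.

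- **That quality of life could never be a time-to-event outcome.** Time to a defined deterioration can be built from repeated scores. The defect is that no such event is defined here.
- **That the repeated scores would be thrown away.** They still feed the utilities for QALYs. Only the estimate of the treatment effect on quality of life is in question. A deterioration cut-off is also only one way in which the text might be followed; the protocol plans none.
- **That hospitalisation is mis-analysed too, because a first-event model ignores repeat admissions.** Time to first admission is a valid Cox outcome. No section defines the outcome as total admissions: the sections on additional consent and on adverse events speak of incidence, which does not settle it. Healthcare use is collected separately, and costs have their own analysis. A recurrent-event model would be a preference, not a correction.

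**Conclusion.** The point holds in a limited form. Section {20a} prescribes Cox regression, with a proportional-hazards check for each model, for a set of outcomes that includes a repeated EQ-5D-5L score with no event defined. The stated model does not fit that outcome as defined.

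The consequence is confined to one secondary outcome and to somewhere between about 3,000 and 6,000 planned follow-up scores before early exits. Those counts describe how much data is concerned; they do not measure bias. The conclusion assumes that the unqualified reference to the secondary outcomes includes quality of life, and that nothing outside the article defines an event for it. An analysis plan that is not shown may already name a suitable model, but the published sentence would still need correcting.

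**What to change.** Limit the Cox sentence, and the proportional-hazards check, to the time-to-event outcomes, and list them, including time to first hospitalisation.

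For EQ-5D-5L utility, name a linear mixed model with random effects for participant and PD unit, and fixed effects for visit, treatment, treatment-by-visit, size category and country. Add two statements:

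- **Death and early exit.** Say how scores after death are treated, and how those missing after transplantation, hemodialysis transfer or withdrawal are treated. A mixed model left to its defaults in effect projects scores beyond death.
- **The score labelled baseline.** Table 1 collects it after training, so the intervention may already have affected it. It should not be entered as a pre-intervention covariate, since adjusting for it could remove part of the effect. Say whether it is treated as one of the outcome measurements or left out of the comparison.

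The cost is a few sentences in the statistical section and the matching text in the analysis plan. It needs no new data, no extra visits and no change to the sample size. It should be settled before unblinded quality-of-life data are examined.

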## Assignment of interventions: Allocation

### Sequence generation {16a}

Random allocation of clusters will be 1:1 according to a computer-generated randomization algorithm using random permuted blocks within strata formed by country (Australia, New Zealand) and center size (small, medium, large, and very large) to minimize the risks of imbalance in baseline participant and center characteristics across different sized clusters.

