### Concealment mechanism {16b}

Allocation will be concealed by holding the stratified random permuted blocks on a password-protected server at the Central Coordinating Center and available only to the trial unblinded statistician.

Due to the type of intervention, allocation is unmasked to the PD nurse trainers and the site contact at the local site.

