### Main study measures {18a}

#### Demographic and clinical information

Participant demographic and clinical data are collected within the ANZDATA and the NZPDR Registries as part of routine Australian and New Zealand clinical practice. Baseline participant data will be extracted from the Registries including age (in years), sex, ethnicity, primary cause of kidney failure, height, weight, co-existing medical conditions (including cardiovascular disease, cerebrovascular disease, peripheral vascular disease, diabetes mellitus, and chronic lung disease), and smoking history. Additional information will be extracted during the enrolment period including kidney failure treatment, peritonitis (undifferentiated between local and systemic cause), tunnel infections and exit site infections, and infection treatment regimens.

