## Discussion

PD-related infections, especially peritonitis is a significant cause of mortality, morbidity, and hemodialysis transfer for patients undergoing PD [21, 23]. PD-related peritonitis rates vary widely across different centers and several studies have reported that this variation is mainly attributed to center-related rather than patient-related factors [22, 26]. In particular, variation may be influenced by differing PD training practices and approaches. Although the ISPD has documented and established guidelines for PD training, significant evidence gaps exist in PD training approaches. Several reviews have highlighted the association between patient training and PD-related outcomes [4, 12, 24]. However, there is no robust evidence evaluating the effectiveness of standardized PD training practices and curricula with regard to PD-related infection or other patient-important outcomes [24].

The TEACH-PD trial aims to provide robust evidence that addresses this evidence gap in PD training. The cluster randomized design of the trial reduces complex care intervention contamination between the intervention and control arms. This study is designed to recruit all patients new to PD and requiring PD training in the participating units. Patients who are established on PD (i.e., prevalent patients) or those with a history of previous exposure to PD training are excluded. The eligibility criteria are deliberately broad to reflect routine clinical practice (i.e., non-English-speaking patients are not excluded). Pediatric patients are excluded as the training modules have not been designed or specifically tailored for their needs. In addition, those patients with a history of receiving PD training are excluded as their learning requirements are expected to be different from those of incident PD patients.

A key outcome of the TEACH-PD CRCT includes the evaluation of the safety, efficacy, cost-effectiveness, and patient-reported experience of a standardized PD training approach and curriculum, compared with current training. With PD-related infections identified as a critical outcome in PD trials, the findings of this study will be disseminated to kidney healthcare professionals and consumers via Kidney Health Australia, Kidney Health New Zealand, publications in peer-reviewed journals, state kidney networks, clinical practice guidelines, and presentations at national and international scientific meetings.

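### Patients are recruited after cluster allocation by sites that know their arm, but the stated Cox models adjust only for unit size and country, so measured recruitment imbalance stays uncorrected

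*Protocol article*

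**What the plan says.** All references are to the protocol article.

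- **Allocation.** Under Sequence generation {16a}: "Random allocation of clusters will be 1:1", in permuted blocks within strata of country and centre size. Trial status reports that all 42 clusters have been randomised.
- **Who knows the arm.** Under Concealment mechanism {16b}: "allocation is unmasked to the PD nurse trainers and the site contact at the local site".
- **Who recruits.** Consent {26a} has trial investigators approach patients. The Induction visit section trains site staff in screening, enrolment and consent at the same session that introduces the curriculum. Recruitment and consent {15} requires individual written consent, with the first approach possible as late as the first training day.
- **When sites start.** Intervention units begin using the curriculum once 75% of eligible trainers are competent. The Discussion acknowledges a lag in activation between the arms.
- **Intended coverage.** The Discussion says: "This study is designed to recruit all patients new to PD and requiring PD training in the participating units".
- **Model.** Under Statistical methods {20a}: "The models will be adjusted for cluster size category and country".
- **Data at hand.** Under Demographic and clinical information: "Baseline participant data will be extracted from the Registries including age (in years), sex, ethnicity, primary cause of kidney failure", followed by height, weight, comorbidities and smoking history.
- **Limitations.** The Discussion names detection bias, performance bias, the activation lag, generalisability and heterogeneous control training. It does not name recruitment bias.

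**The concern.** Randomising units balances, in expectation, what is fixed before allocation: the units and the population each one serves. It does not balance what happens afterwards. If staff who know the arm approach patients differently, or patients respond differently to the training on offer, the enrolled samples can differ between arms even though the units were well randomised. A later start in one arm adds a calendar-time difference in who is available to enrol.

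The two adjustment factors are properties of the unit. They cannot correct a difference in, say, age or diabetes among those enrolled within units. The trial aims at high-certainty evidence on a 20% hazard reduction. A modest difference in case mix could make up a noticeable part of such an effect, or hide part of it. The direction cannot be predicted from the document.

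**Working it through.** **1. The plan's own sample size, as a baseline.** Sample size {14} states a design that "requires 42 clusters to achieve 80% power to detect a 20% reduction in the hazard of a first PD-related infection", with 53% of controls infection-free, an intra-cluster correlation (ICC) of 0.001, and "an average cluster size of 37 incident participants over 2 years". A two-sided 5% level is assumed.

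- Schoenfeld events for HR 0.80: 631.
- Design effect: 1 + (37 − 1) × 0.001 = 1.036, so 631 × 1.036 = 654 events.
- Infection-free under treatment: 0.53^0.8 = 0.602. Mean event proportion: 1 − (0.53 + 0.602)/2 = 0.434.
- Participants: 654/0.434, about 1,506. Clusters: 1,506/37 = 40.7, rounded up to an even 42.

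This agrees with the stated 42 clusters, about 1,500 participants and about 650 events. The sample size is not at issue.

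**2. Order of events against the model.**

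| Step | Effect on balance |
|---|---|
| Units allocated within country and size strata | Balances units in expectation |
| Trainers and site contact learn the arm | Recruitment is no longer masked |
| Site staff screen and patients consent one by one | Enrolment can depend on the arm |
| Intervention sites open later | Enrolment periods differ by arm |
| Cox models adjusted for size and country | Corrects for none of the last three steps |

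**3. How much an imbalance could matter.** The document gives no hazard ratio for any baseline factor, so these inputs are assumed: a binary factor with hazard ratio x of 1.3 or 1.5, prevalence 45% in one arm, and a prevalence higher by d = 5 or 10 points in the other. To a first approximation the treatment HR is multiplied by

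(1 + (x − 1)(0.45 + d)) / (1 + (x − 1) × 0.45).

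The target is |log 0.80| = 0.2231.

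| x | d | Ratio | Log ratio | Share of target |
|---|---|---|---|---|
| 1.3 | 0.05 | 1.150/1.135 = 1.013 | 0.0131 | 6% |
| 1.3 | 0.10 | 1.165/1.135 = 1.026 | 0.0261 | 12% |
| 1.5 | 0.05 | 1.250/1.225 = 1.020 | 0.0202 | 9% |
| 1.5 | 0.10 | 1.275/1.225 = 1.041 | 0.0400 | 18% |

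In the largest case, with 650 events and the design effect above, the shift in the test statistic is √(650/1.036/4) × 0.0400 = 0.50. The two-sided type I error then rises from 5% to about 8%. The smallest case leaves it at 5.3%.

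**The case against.** The strongest reply is that adjusting for the randomisation strata is right, that this is a condensed article, and that further adjusted analyses commonly sit in a statistical analysis plan not shown here. Baseline characteristics will also be presented by group, so a measured imbalance would be visible. The first part stands: the strata should stay. The rest does not dispose of the point. {20a} states the adjustment set rather than leaving it open, and the planned sensitivity analyses under {20c} concern protocol deviations and missing values. Seeing an imbalance does not correct it, and covariates chosen after seeing it are open to challenge.

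A second reply is that all eligible patients able to consent are to be invited in both arms. Complete invitation would reduce the risk, but consent can still differ by arm, and the article does not mention counts that would show whether invitation was complete.

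Some stronger readings are tempting, and the document does not support them:

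- **That enrolment is shown to be far from complete.** 42 × 18.5 a year × 4 years = 3,108, and 1,500/3,108 = 48%. That needs every unit open for the whole July 2019 to June 2023 window at the 2014–2015 intake. Unit opening dates are not given. A mean open time of 3 years gives 64%, and 2 years gives 1,500/1,554 = 97%. A low overall fraction would in any case not show a difference between arms.
- **That adjusting for each unit's earlier peritonitis rate would recover substantial precision.** Gains of 13% to 24% follow only from an assumed centre log-hazard variance of 0.05 to 0.10 and an assumed correlation of 0.8 between past and trial-period rates. At the stated ICC of 0.001 (variance about 0.0024) the same calculation gives about 0.1%.
- **That the listed covariates are known predictors of infection.** The article lists them as registry variables only. Its Background says that centre-related factors outweigh patient-related ones in peritonitis variation.
- **That adjustment removes recruitment bias.** It acts on measured factors only.

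**Conclusion.** The point holds in a limited form. The design allows enrolment to differ between arms, and the stated model makes no use of the collected patient data that could correct the measured part. This is an avoidable weakness in a stated analysis choice; it is not evidence that the trial is biased.

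The size is conditional. Under the assumed hazard ratios, prevalence and imbalances, the treatment HR moves by 1.3% to 4.1%, or 6% to 18% of the target log hazard ratio. The figures are for one factor; several imbalances could add up or cancel. If enrolment is balanced in practice, the change does little to the estimate beyond making it conditional on the covariates.

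**What to change.** 1. In the Cox model for the primary outcome, keep cluster size category and country and add a short pre-specified set of patient covariates already collected, for example age, sex, ethnicity, diabetes and cardiovascular disease. Report the strata-only model alongside. The clustered log-rank comparison can stay as the unadjusted one.
2. Report the numbers eligible, approached and consented by arm.
3. Name recruitment bias in the limitations.
4. Compare enrolled with all incident patients, or weight to that population, only if ethics approval permits use of non-participants' registry data. The article does not show that it does.

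The cost is mainly analysis-plan wording and the by-arm screening counts. There are three drawbacks. The hazard ratio becomes conditional on the covariates, so some gap from the strata-only estimate is expected even without imbalance and should not alone be read as bias. A rule for missing covariates is needed. Unmeasured differences in who was enrolled remain.
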